## Survey variables

The case record forms allow the recording of laboratory values and clinical findings usually recorded during the diagnostic procedures for virus hepatitis.

The headings provided for this purpose do not mean that all parameters need necessarily be investigated.

If the data are recorded, however, they should be documented completely in order to increase the evidential value of this noninterventional study.

The following parameters can be documented in this observational study:

### Practice characteristics (multiple responses possible)

– These data are updated every six months:

- Member of the Association of German Resident Gastroenterologists (BNG) yes/no
- Type of facility
- single, group practice, specialized practice, hospital outpatient department, university hospital outpatient department
- Physicians in the participating practice/outpatient department:
- general practitioner, internal specialist, gastroenterologist, hematologist / oncologist, infectious diseases specialist, addiction medical specialist, psychiatrist, other.
- Number of patients cared for last year with:
- HCV, HBV or HIV infection, HIV/HCV and HIV/HBV coinfection, opioid substitution, post liver transplantation
- Regular cooperation with:
- psychiatrists / psychologists / ext. DCC
- internal specialists, surgeons, institutes/outpatient departments, detoxification

Physicians performing substitution:

- Regular monitoring of concomitant use:
- alcohol monitoring / quarterly, visual urine testing / quarterly
- Patient substitution status (number):
- methadone, buprenorphine, polamidone, other
- Maintenance, attitude towards cessation, detoxification (absolute or in %)

### Main module for recording treatment of hepatitis C

Important: parameters of particular importance in various modules are also presented there. To prevent documentation errors, such values are presented in all modules independently of the module in which they are entered.

#### Baseline examination

- Written patient informed consent (date)
- Patient data for age, gender, height, weight (BMI is calculated automatically from the latter two parameters), ethnicity, speech communication and first language learned (German, Turkish, Russian, Polish, Italian, other)
- Patient's insurance status: statutory health insurance, private health insurance, self-pay patient
- First three characters of the postal code of the patient's residence
- Concomitant diseases

| Psychiatric illness e.g. depression, psychosis, status post attempted suicide, currently with/without treatment | Inflammatory bowel disease |
| --- | --- |
| Cardiovascular: arterial hypertension, CHD/angina pectoris, myocardial infarction, PAOD | Hepatitis A |
| Malignant diseases: Hodgkin, non-Hodgkin (incl. lymphatic leukemia), skin tumours | Hepatitis B |
| Diabetes mellitus | Acquired immune weakness (AIDS/HIV)*: anti-HIV-IgM |
| Chronic respiratory tract diseases: asthma, COPD | Thyroid dysfunction: hypofunction hyperfunction |
| Inflammatory joint disease (including rheumatism) | Arterial vascular disease |
| Lipid metabolism disorders | Skin disease psoriasis  neurodermatitis |
| Alcohol abuse / dependence | Syphilis |
| Drug abuse: active drug misuse (intravenous / other) drug substitution therapy (methadone, polamidone, buprenorphine, heroin, other) status post drug misuse | TBC |
| Liver function disorder | Herpes zoster |
| Renal insufficiency | Dental and peridental diseases, e.g. caries |
| Lipid distribution disorder | Allergies |
| Ophthalmological diseases e.g. retinopathies, retinal vascular occlusions | Status post organ transplantation: liver, kidney lung, heart |
| Neurological diseases e.g. convulsions | Other |
| Polyneuropathy |  |

- Route of transmission of hepatitis (mode of infection): blood products, illicit drugs (intravenous / nasal), sexual transmission, tattooing / piercing, needle stick injury, surgical / medical intervention, medical / dental staff, dialysis, unknown, other

Medical history: naive;
 Relapser/nonresponder to previous treatment with: IFN monotherapy
 IFN-RBV combination therapy

PEG monotherapy
 PEG-RBV combination therapy
 Reason for relapse / nonresponse: virological nonresponse
 inadequate previous treatment
 intolerability

- Estimated duration of infection:
- Clinical symptoms / laboratory values at first diagnosis that led to the diagnosis "chronic hepatitis C": none, fatigue, fever, muscular stiffness, skin changes, hair loss, joint pain, muscle pain, abdominal pain, nausea, reflux, weight loss, headache, insomnia, irritability, restlessness, depression, depressive mood, psychosis, impaired concentration, anorexia, jaundice, pruritus, elevated GPT, craving / withdrawal-like symptoms, other:
- Laboratory parameters
  GPT (=ALT), GOT (= AST), gamma-GT
  Other laboratory parameters:
  Hemoglobin, RBC, platelets, WBC, neutrophils (%), TSH, Quick's value, AP, bilirubin, creatinine, serum ferritin, serum iron, transferrin, alpha fetoprotein, albumin, blood glucose (fasting), HbA1c, triglycerides, cholesterol (total), HDL, LDL, uric acid, CRP quantitative.
- Hepatitis C laboratory diagnostic tests:
  HCV-PCR (qualitative/quantitative)
  Anti-HCV
- HCV genotype
- Hepatitis B laboratory diagnostic tests: HBsAg (+/-), anti-HBc (+/-), if +, then anti-HBc-IgM; if HBsAg+, then HBeAg +/-; HBV-DNA quant./qual., HBV genotype, anti-HBs (+/-); anti-HDV (+/-), if +, then HDV-RNA (+/-, qual. or quant.)
- Autoantibodies: ANA, LKM, SMA, AMA, SLA, Trak, MAK, rheumatoid factors, other
- Vaccination status/vaccination protection against hepatitis A and B: yes/no
- Clinical examination:
  – ultrasound: normal findings, splenomegaly, picture of chronic liver disease, fatty liver, sonographic signs of liver cirrhosis, result unknown since performed by physician providing previous care
  – histology: date performed; stage of fibrosis and degree of inflammatory activity after selection of score
  – fibroscan (kPa)
- Clinical findings:
  Normal findings, spider naevi, cirrhosis (Child-Pugh classification), hepatic encephalopathy, esophageal varices, ascites
- Alcohol consumption no/yes, if yes, then inquiry  / > 40 g/day and drinks/day in the last 30 days
- Assessment of the patient's quality of life impairment by hepatitis C: none, slight, moderate, severe
- Questions on repeated documentation in this or a previous online observational study in the BNG
- Start of treatment
- Initial dose of peg­interferon alfa-2a (Pegasys®): 180 µg, other dosage
- Treatment with ribavirin, e.g. Copegus®: 800, 1000, 1200 mg/day, other dose, dose schedule
- Concomitant therapy
- Submission of the SF-36 and sociodemography record form before therapy (questionnaire to be completed by the patient)
- Pregnancy test
- Contraception

#### Examination after 2 weeks

- Laboratory parameters
  GPT (=ALT), GOT (= AST), GGT
  Other laboratory parameters:
  hemoglobin, platelets, WBC, neutrophils (%), bilirubin
- Adverse events (including suspected cases) with substance-specific causality survey
- Date and dosage information for peg­interferon alfa-2a (Pegasys®): 180 µg and ribavirin, e.g. Copegus® (including dose changes and rationale for change, dose schedule)
- Concomitant medication
- New comorbidities
- Clinical symptoms: none, fatigue, fever, muscular stiffness, skin changes, hair loss, joint pain, muscle pain, abdominal pain, nausea, reflux, weight loss, headache, insomnia, irritability, restlessness, depression, depressive mood, psychosis, impaired concentration, anorexia, jaundice, pruritus, elevated GPT, craving / withdrawal-like symptoms, other;
  causal relationship with Pegasys and/or ribavirin
- Treatment-related sick leave (duration) since the last examination
- Pregnancy test

#### Examinations during treatment in week 4, 8, 12, 24, 36 and 48

- *Only in week 12, 24, 36 and 48:* body weight
- Laboratory parameters
  GPT (=ALT), GOT (= AST), GGT,
  Other laboratory parameters:
  hemoglobin, platelets, WBC, neutrophils (%), bilirubin, creatinine
  *Only in week 12, 24, 36 and 48*: TSH, blood glucose (fasting), HbA1c*Only in week 24:* ANA, LKM, SMA, AMA, SLA, Trak, MAK, rheumatoid factors
- Hepatitis laboratory diagnostic tests
  HCV-PCR (quantitative/qualitative), *in week 4 and 12 recommended*
  HCV-PCR (qualitative), *only in week 24* for GT-2/3, o*nly in week 48 for GT-1/4 recommended*
  (HCV-PCR (quantitative/qualitative) can be documented in week 4, 8, 12, 24 and 48)
- Adverse events (including suspected cases) with substance-specific causality survey
- Date and dosage information for peg­interferon alfa-2a (Pegasys®): 180 µg and ribavirin, e.g. Copegus®: (including dose changes and rationale for the change, dose schedule)
- Concomitant medication
- New comorbidities
- Clinical symptoms: none, fatigue, fever, muscular stiffness, skin changes, hair loss, joint pain, muscle pain, abdominal pain, nausea, reflux, weight loss, headache, insomnia, irritability, restlessness, depression, depressive mood, psychosis, impaired concentration, anorexia, jaundice, pruritus, elevated GPT, craving / withdrawal-like symptoms, other;
  causal relationship with Pegasys and/or ribavirin
- Treatment-related sick leave (duration) since the last examination
- (Monthly) pregnancy test
- *Only in week 12, 24, 36 and 48:*
  Clinical assessment of the tolerability of Pegasys and the combination with ribavirin (Copegus®): very good, good, moderate, poor,
- *Only in week 12, 24, 36 and 48:*
  Compliance (assessed by the physician):
   very good: all medications taken
   good: max. 10% not taken
   satisfactory: max. 20% not taken
   poor: > 20% not taken
- *Only in week 12, 24, 36 and 48:*
  Quality of life assessment compared to before treatment: symptom-free; improved, but not symptom-free; unchanged
- *Only in week 12, 24, 36 and 48:*
  Alcohol consumption no/yes, if yes, inquiry  / > 40 g/d and drinks/d in the last 30 days
- *Only in week 12:* *Submission of the SF-36 and sociodemography record form (questionnaire to be completed by the patient)*

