### Hepatitis C

Chronic virus hepatitis C is a disease which often takes a clinically insidious course and threatens the affected patients mainly because of its late complications (liver cirrhosis, hepatocellular cancer). In June 2002, peg­interferon alfa-2a (Pegasys®) was approved for the treatment of chronic virus hepatitis C by the European Agency for the Evaluation of Medicinal Products (EMEA) on the basis of two international marketing authorization studies (Zeuzem et al. 2000, Heathcote et al. 2000).

In patients with chronic hepatitis C, Pegasys® is best used in combination with ribavirin.

Since January 2003, ribavirin Copegus® has been approved by the Federal Institute for Drugs and Medical Devices (BfArM) in Germany for combination with peg­interferon alfa-2a (Pegasys®) in the treatment of chronic hepatitis C.

The combination of Pegasys® and ribavirin is indicated in non-pretreated patients and in patients who have failed to respond to previous treatment with interferon alfa (pegylated or non-pegylated) alone or in combination therapy with ribavirin.

Monotherapy with peg­interferon alfa-2a is indicated mainly when there is intolerance or contraindications to ribavirin.

Pegylated interferon alfa-2a (Pegasys®) is administered to patients with genotype 1 and the more rarely occurring genotypes 4, 5 and 6 in the combination with ribavirin initially for 12 weeks. The decision whether to prolong the therapy by 36 weeks to altogether 48 weeks or to discontinue the treatment is based on an HCV-RNA assay: either the virus assay in week 12 is negative (equivalent to a reduction in the viral load below the limit of detection) or a reduction was achieved in the original serum HCV-RNA by 2 log steps (equivalent to 99 % of the baseline value before start of treatment).

Patients who did not show this defined "early virological response" (EVR) after 12 weeks will with very high probability (97 %) also not have any lasting therapeutic success after further treatment (Ferenci P et al. 2001, Fried MW et al. 2001). This procedure saves the patient unnecessary stress from treatment side effects and saves costs.

In patients with genotypes 2 or 3, on the other hand, such a high EVR of 97 % is achieved that no monitoring of the viral load after 12 weeks is recommended.

As regards the duration of treatment, a further multicentre international study for patients with genotypes 1 and 4 also confirmed a treatment duration of 48 weeks (Hadziyannis SJ et al. 2004).

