## Analysis plan

The descriptive statistical evaluation is performed by the company factum GmbH.

All recorded data – depending on the type of characteristics – are presented descriptively as mean, standard deviation, minimum, maximum, median, 1st and 3rd quartile or their frequency distribution. Categorical characteristics are presented with absolute and relative frequencies within the individual categories.

For continuous variables multiply recorded over time, basic statistics with absolute differences between the end of observation and the baseline value are calculated.

For the tolerability analysis, adverse drug reactions are counted by frequencies using the respective preferred terms categorized according to organ systems. These survey tables are additionally stratified according to the clinical relevance of the drug effect as "serious/non-serious".

Moreover, an assessment of the clinical tolerability of the hepatitis C therapy is performed by the physician.

For the safety laboratory analysis, basic statistics over time are generated per parameter. Additionally, the frequencies of changes in categorical laboratory values (classified into "normal", "increased", "reduced") are presented per laboratory parameter between the baseline value and end of treatment and between the end of treatment and follow-up.

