The practice characteristics can be documented once per calendar year. A documentation effort of EUR 20.11 is reimbursed for this with a factor of 1.15 in accordance with GOÄ 80. Whether this amount is reimbursed to the participating physician or study assistant is regulated in the contract concerning the performance of the NIS.

For the administration and explanation effort required for the quality of life questionnaires SF36 to be completed by the patient and the sociodemography questionnaires at 4 time points during the therapy (baseline examination, week 12, end of treatment/documentation, week 24 follow-up), a reimbursement amount of EUR 2.50 is paid per form, i.e. EU 10.00 for one complete set of questionnaires per patient. Whether this amount is reimbursed to the participating physician or the study assistant is regulated in the contract concerning the conduct of the NIS.

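### The repeated quality-of-life change item has no *worse* option, so this one item can show only improvement or no change

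*Protocol*

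**What the plan says.** In the main module (Protocol 7.2.2) the documented item is "Quality of life assessment compared to before treatment: symptom-free; improved, but not symptom-free; unchanged". It is listed once for weeks 12, 24, 36 and 48, twice at end of treatment and once at follow-up week 24, with the same three options each time.

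The baseline item is a different scale: "Assessment of the patient's quality of life impairment by hepatitis C: none, slight, moderate, severe". It is not repeated at any later visit.

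The patient-completed SF-36 is collected "at 4 time points during the therapy (baseline examination, week 12, end of treatment/documentation, week 24 follow-up" (section 11, consistent with the visit lists in 7.2.2).

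From week 12 to end of treatment the form also carries a rating with a negative end: "Clinical assessment of the tolerability of Pegasys and the combination with ribavirin (Copegus®): very good, good, moderate, poor". Symptoms and adverse events are documented at every visit after baseline.

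Section 8.3 states that "Categorical characteristics are presented with absolute and relative frequencies within the individual categories", and section 9 commits the report to a descriptive presentation of every recorded variable.

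**The concern.** An item that asks for change since before treatment needs a category for each direction of change. This one has two favourable options and one neutral option. Worsening on treatment is foreseeable from the protocol itself. In explaining the week-12 stopping decision, section 4.1.3 says: "This procedure saves the patient unnecessary stress from treatment side effects and saves costs". The visit forms also list symptoms to be judged for a causal link to either drug, and they record treatment-related sick leave.

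A patient who feels worse has no truthful answer. Following the plan as written gives a quality-of-life table that can show only benefit or no change, in a study whose main objective includes tolerability. The category was never collected, so an analysis plan could not restore it.

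**Working it through.** The plan rests no figure on this item, so there is nothing to reproduce. The check sets the instruments side by side and then illustrates the direction of the distortion.

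**Schedule (Protocol 7.2.2 and 11)**

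| Time point | Change item | *Worse* option | SF-36 due |
| --- | --- | --- | --- |
| Week 12 | yes | no | yes |
| Week 24 | yes | no | only if treatment ends about then |
| Week 36 | yes | no | only if treatment ends about then |
| Week 48 | yes | no | only if treatment ends about then |
| End of treatment | yes, listed twice | no | yes |
| Follow-up week 24 | yes | no | yes |

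The item is used at 6 time points, and 0 of 6 offer a negative category. The SF-36 coincides with 3 of the 6.

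**Where the gap is widest.** The Synopsis describes courses of 24, 48 and 72 weeks, and end of treatment carries an SF-36.
- 24-week course: end of treatment falls at about week 24, so an SF-36 is due then.
- 48-week course: weeks 24 and 36 have no SF-36; week 48 is about end of treatment.
- 72-week course: weeks 24, 36 and 48 have no SF-36.

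**Can change be rebuilt from baseline?** No. The baseline item grades severity of impairment on four levels and is asked once. The later item grades change on three. The two cannot be subtracted.

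**Direction and possible size (assumed shares, not from the documents).** Let i be the true share improved (including symptom-free) and w the true share worse, with i = 0.20.
- Worse entered as *unchanged*: reported improved = i = 20%, and reported unchanged = 1 − 0.20 = 80%, whatever w is. With w = 0.40 the true unchanged share is 1 − 0.20 − 0.40 = 40%.
- Worse left blank: reported improved = i / (1 − w).
  - w = 0.10: 0.20 / 0.90 = 22%
  - w = 0.40: 0.20 / 0.60 = 33%
  - w = 0.60: 0.20 / 0.40 = 50%

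Reported worsening is 0% in every case. The mechanisms differ: merging leaves the improved share correct but hides worsening inside *unchanged*, while blanks inflate the improved share.

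**Which mechanism is likelier?** Section 7.2 does not require every parameter to be investigated, which allows blanks. Section 11 withholds the fee for a visit that stays incomplete, which favours entering something. The protocol does not say whether a blank here makes a visit incomplete, so the mix is unknown.

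**What an eCRF change can still reach.** This version is dated 28.02.2013 and planned last patient in was 31/12/2011. For a course begun that day, week 48 falls 48 × 7 = 336 days later, on 1 December 2012. If recruitment closed as planned, the scheduled visits up to week 48 were past. What remains is mainly the end of 72-week courses and follow-up visits.

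**The case against.** The strongest reply is that the study does record deterioration. SF-36 change is available at week 12, end of treatment and follow-up. Symptoms, adverse events with causality, sick leave and a tolerability rating down to *poor* cover related harm, and lack of tolerability is a listed reason for stopping. Quality of life is neither a stated objective nor among the Synopsis's main parameters of interest. The evaluation is descriptive, and no sample size or virological outcome depends on this item.

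All of that stands and sets the scope. A reader might infer from the missing category that the study cannot detect worsening on interferon, or that this item is the only quality-of-life measure for everyone at weeks 24, 36 and 48. The documents support neither: the other instruments exist, and many patients who finish at about week 24 or 48 have an end-of-treatment SF-36 due then.

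The reply does not rescue the item itself. It is still collected at six time points and, under sections 8.3 and 9, will be tabulated and reported. A lost line in the PDF text is unlikely, since all four listings have the same three options.

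**Conclusion.** The point holds for this single item. Its frequency table is one-sided in favour of treatment by construction, and *unchanged* is a mixture of stable and worse patients that cannot be separated. The loss is greatest at on-treatment visits without an SF-36: mainly weeks 24 and 36 of longer courses, and week 48 of 72-week courses. Severity is minor to moderate.

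No count of affected patients can be given. A reader might apply an assumed worsening rate to the planned 9000, but the documents give no such rate, and shortened courses and discontinuations mean that not all patients reach the later visits. The percentages above show direction and sensitivity only.

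Two assumptions remain. The first is that the item had these options throughout data collection, since earlier protocol versions are not shown. The second is that recruitment closed on the planned date, which affects only how much the form change can still achieve.

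**What to change.** **Reporting rule, which carries most of the benefit.** For data already entered, label the third category *unchanged or worse*, and show the number of blanks at each visit beside the percentages. Do not present the item as quality-of-life change. Base quality-of-life conclusions on SF-36 change from baseline. The cost is a table label, a footnote and a sentence in the report.

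**Form change.** Add a *worsened* option for any visits still to come, and tabulate those records separately because old and new formats cannot be pooled. Delete the second end-of-treatment listing. The cost is one eCRF option. The yield is small, because most of the remaining visits already have an SF-36 scheduled.

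Repeating the baseline item at later visits would not solve the problem. It asks about impairment caused by hepatitis C, so a patient made worse by treatment could properly be scored as having little or none.

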#### At the end of treatment / documentation (end of therapy):

- Therapeutic consequence: reason for end / discontinuation of therapy
- Reasons for therapy discontinuation: lacking virological response, lacking tolerability, lacking compliance, unplanned event (e.g. imprisonment, detoxification), patient's wish, patient no longer attended, other reason
- Concomitant medication
- New comorbidities
- Body weight
- Hepatitis C laboratory diagnostic tests
  HCV-PCR (quantitative/qualitative), *only recommended in week 12*
  HCV-PCR (qualitative), *only recommended in week 24 for GT-2/3, only in week 48 for GT-1/4*
  (HCV-PCR (quantitative/qualitative) can be documented in week 4, 8, 12, 24 and 48)
- Hepatitis B laboratory diagnostic tests (only if chronic hepatitis B was documented at the baseline examination): HBsAg (+/-), HBeAg +/-; HBV-DNA quant./qual., anti-HBs (+/-); anti-HDV (+/-), HDV-RNA (+/-, qual. or quant.)
- Autoantibodies: ANA, LKM, SMA, AMA, SLA, Trak, MAK, rheumatoid factors, other
- Laboratory parameters
  GPT (=ALT), GOT (= AST), GGT,
  Other laboratory parameters:
  hemoglobin, platelets, WBC, neutrophils (%), bilirubin, creatinine, TSH, blood glucose (fasting), HbA1c, triglycerides, cholesterol, HDL, LDL, serum ferritin
- Clinical symptoms: none, fatigue, fever, muscular stiffness, skin changes, hair loss, joint pain, muscle pain, abdominal pain, nausea, reflux, weight loss, headache, insomnia, irritability, restlessness, depression, depressive mood, psychosis, impaired concentration, anorexia, jaundice, pruritus, elevated GPT, craving / withdrawal-like symptoms, other;
  causal relationship with Pegasys and/or ribavirin
- Treatment-related sick leave (duration) since the last examination
- (Monthly) pregnancy test
- Adverse events (including suspected cases) with substance-specific causality survey
- Clinical assessment of the tolerability of Pegasys and the combination with ribavirin (Copegus®): very good, good, moderate, poor
- Quality of life assessment compared to before treatment: symptom-free; improved, but not symptom-free; unchanged
- Alcohol consumption no/yes, if yes, inquiry ≤/ > 40 g/d and drinks/d in the last 30 days
- Compliance (assessed by the physician):
   very good: all medications taken
   good: max. 10% not taken
   satisfactory: max. 20% not taken
   poor: > 20% not taken
- Quality of life assessment compared to before treatment: symptom-free; improved, but not symptom-free; unchanged
- Submission of the SF-36 and sociodemography record form (questionnaire to be completed by the patient)

